#### Data collection

Based on the categories of participants (patients/families, primary care professionals, specialists, decision-makers), four data collection strategies will be used within in-depth multiple case studies with embedded levels of analysis [56]. The proposed strategies are as shown in Table 2:

a. Focus groups (FG) to examine opinions and reactions and to establish a collective understanding of the evaluation aspects proposed [57]. These FG will be conducted by an experienced interviewer using interview guides with open-ended questions developed for each level of analysis, in order to obtain information on the identified dimensions;

b. Semi-directed individual interviews (II) conducted with specialist physicians and CDPM professionals;

c. Patient files (5 per clinic) will be reviewed, using an extraction grid. This review will serve both to clarify how the range of services at the level of patients has been operationalized, and to highlight elements of services integration;

d. Analysis of documentation: Several documents produced during the intervention implementation (checklist for the intervention fidelity report, summaries of team meetings, etc.) will be analyzed to provide an in-depth understanding of the various contexts in which the intervention was deployed, in order to elucidate the positive elements and barriers that were encountered: committee meeting reports, the clinical project coordinator’s notes, internal and external announcements to various professional and non professional communities, etc.

##### Data analysis

The data collected from all participants (patients/families, primary care professionals, specialists, decision-makers) during individual interviews and focus groups (transcription of audio recordings and observer notes) will be analyzed using content analysis. Following an inductive approach combined with thematic analysis, these analyses will be done in three steps to identify emerging themes and trends. The first step is the “coding” which consists of reading and analyzing the corpus. Data management software (NVivo 9.0, QSR Int. USA) will be used to identify units of meaning that will be grouped into nodes that will help extract information related to the same subject. The second step is “sorting” the information into codes or code combinations that will be reviewed and sorted according to different contexts. This information can then be broken and grouped differently from the original version. The last step is “analysis” that will be done throughout and after the coding process. This phase will allow us to analyze all the coded extracts from various documents. In addition to revealing the specific elements of each of the implementation assessment dimensions that were chosen, analysis at this stage will specifically seek to deepen our understanding of the interaction between the intervention, its context and its effects. Contextual determinants of the changes will be investigated using various explanatory models, including political, structural and psychological ones [48,58].

#### Evaluation of effects (objective 2)

Effects will be assessed using three different strategies. To measure short-term effects, a pragmatic randomized experimental design with delayed intervention in the control group will be used [59]. The first step of randomization is the sequence generation using a simple random allocation sequence. The second step is allocation concealment by development and allocating concealment mechanism (sequentially numbered, sealed, opaque envelopes) followed by preparation of the allocation concealment mechanism using the sequence from step one. Research team members involved in generation and allocation concealment will be different from the team members involved in the implementation of assignments. Thus, the intervention group allocation system is set up so that the team member enrolling participants does not know in advance in which group the next person will be allocated.

Patients will be referred by primary care providers (family physician or nurse) to the research team who will be responsible for assessing eligibility and obtaining informed consent, as well as baseline measures (T1). For each study participant, a research assistant at the central office will open a numbered and sealed envelope. The card inside will tell if the patient will be in group A or in group B. This information will immediately be provided to the patient and subsequently to the clinical team in order to schedule the clinical interventions.

Because participants will be invited to receive the interventions in their usual clinics, blind randomization is not possible. Both patients and health care providers will know who is involved in each group, therefore we used independent (unmatched) random samples of patients to receive the intervention immediately after baseline assessments (Group A: immediate intervention group) or at the end of a three-month waiting period (Group B: delayed intervention group). We chose this randomization process because of the potential proximity of patients in and between clinics. In practice, however, we think that communication between patients of the same clinic or between clinics is scarce and will not pose a substantial threat for contamination.

Since it is possible that participants in different groups and phases might come in contact with each other as many will be recruited in the same practice, some precautions will be taken in order to minimize the before and after evaluation biases. To prevent selection bias, the rigorous randomization methodology and allocation concealment process described previously will be respected throughout the project. The methods were reviewed and approved by the Research Ethics Board of the CSSSC and the measurement tools were validated. We expect a response rate greater than 80% and baseline measurements will be comparable in the sense that no significant differences will exist between the groups with respect to age, gender and pre-test measurements. If necessary, the statistical models will be adjusted to ensure comparability of the groups. Each subject intervention will last less than three months and the clinical intervention period is limited to 12 months in order to ensure a contemporaneous data collection.

As stated in the logic model, with the three-month delay design we seek to examine: (1) whether the immediate intervention group (Group A) will have changes at 3 months that are sustained; (2) whether there will be changes in the first 3 months before the intervention with Group B; (3) whether the short-term results of Group A will be different from those of Group B; and (4) whether the outcomes of Group A can be sustained one year later. Theoretically, it is anticipated that these short-term results in attitudes and behaviors of patients will be the precursors of the mid-term changes expected in the maintenance of a healthy lifestyle, quality of life and psychological well-being.

In each clinic where the intervention will be deployed, patients eligible to receive the intervention must be between 18 and 75 years of age and present at least one of the following conditions: diabetes, cardiovascular disease, chronic obstructive pulmonary disease (COPD), asthma or risk factors (smoking, obesity, dyslipidemia, glucose intolerance, and metabolic syndrome). Patients with serious cognitive problems will be excluded.

The decision to explore all these chronic conditions together was preferred to the single disease design for many reasons. The first reason is that this project is an adaptation of CD specialized services already deployed in the region for these chronic conditions into an integrated network. Although these services have often been cited as an example of the successful integration of CDPM services, this approach still faces several challenges requiring a review of its operations and organization to better reflect the reality of patient follow-up and needs. To ensure greater accessibility and better post-intervention continuity, it has been noted that closer collaboration with primary care professionals such as family physicians and nurses from various primary care settings will be necessary in the next few years. Thus, all services for patients with a CD could be provided in an integrated and ongoing fashion. The second reason is that multifaceted interventions are more effective than single ones [60], and sustainable change requires a multi-level approach especially when multiple interventions at varying levels are interlinked and mutually reinforced to maximize the impact on patient behaviour, life-style and self-management. This approach involves action at the patient, practitioner, health care provider and service organization levels in delivery and support. This study aims to provide guidance to patients through trained practitioners working within a health care system that must be responsive to long-term patient needs through its services and patient-centered approach. Accordingly, we have adapted the CDPM professional training so the interventions can be delivered in primary care settings. The selection of these targeted CD (diabetes, cardiovascular disease, asthma, COPD and risk factors for these diseases) is based on a pragmatic approach that aims to enrol patients whose characteristics are similar to those most frequently seen in primary health care settings.

To comply with the pragmatic nature of the intervention, it is up to the referring professional (primary care physician or nurse) to determine eligibility. For each patient, the referring professional will request the patient’s authorization to disclose his or her contact information to the research team and then complete a referral form. Patients refusing to take part in the study will still be eligible to receive the intervention without being involved in the evaluation process. Two patients from the same family can receive the intervention, but only one (randomly selected) will be asked to participate in the research project.

Patients agreeing to participate will complete an initial set of questionnaires at baseline (T1) collecting the main variables and sociodemographic data. Patients will be randomized to receive either the intervention within a short period of time (Group A) or later (three months later for Group B). At time 2 (T2), which will occur three months after the intervention for Group A or immediately before the intervention for Group B, patients will complete the second evaluation questionnaire. Baseline measures will be used to document equivalence between groups while T2 measures will enable the assessment of the effect after three months. A short questionnaire documenting co-interventions will also be administered at T2 (Table 3). Co-interventions represent any additional health care or CDPM services and/or therapeutic procedures other than those that are formally included in the study and may introduce confounding variables that could potentially affect the validity of the results of this study.

**Table 3 T3:** Variables and outcome measures

**Short-term:** Key measurements of effect (measured at T1 and T2 in Groups A and B)	
Self efficacy	The Self-Efficacy for Managing Chronic Disease (SEM-CD) scale (6 items) developed by the Stanford Patient Education Research Center [67].
Empowerment	Proxy of “The Health Education Impact questionnaire (heiQ)” [77]
Comorbidity	The Disease Burden Morbidity assessment (DBMA) [64]
**Mid-term:** Key measurements of effect (measured at T1 and T3 in Groups A and C)	
Health behaviour	Behaviour Risk Factor Survey System Questionnaire (eating habits, physical activity, smoking and alcohol consumption) [65]
Functional health status/quality of life	SF -12 [63,78]
Psychological well-being	K-6 [62]
Comorbidity	The Disease Burden Morbidity Assessment (DBMA) [64]

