To ensure fidelity of the intervention and to prevent clustering, the intervention was designed by the research team. Nevertheless, in this regard the research team consulted with primary health care providers in each practice, specialists, and decision-makers to ensure that the intervention is adapted to the needs expressed. Moreover, interventions will be done by CDPM professionals, recruited and trained by the research team about the general principles of self-management support, patient-centered care, motivational interviewing, interprofessional collaboration and integration of services. The rationale of such a process is to ensure standardization of practices within and across the eight clinics in order to prevent study interventions from evolving differently, as results will be unusable if participants experience different interventions. However, despite the use of such patterns, heterogeneity that may be observed and documented between clinics in terms of outcomes produced, termed “center effects” is part of the pragmatic design and will reflect the clinical reality of primary health care. It has been suggested that interventions may be affected by center-specific issues and characteristics such as degree of sub-specialization within practices and provider background and experience, [52] however, we believe that delivering interventions by practitioners who evolve through the same training process will reduce clustering effects so that the experiment can be replicated across centers and over time [53]. This desired objectivity is based on the involvement of systematic recourse to the collective production of evidence and requires standardization of practices within settings in order to produce replicable findings which can then be used to standardize practice within, and across, clinical care settings [54]. Moreover, efforts will be made to increase the number of participants in each setting in order to reach a certain degree of comparable statistical weight for every practice. Throughout the implementation phase, information about interventions offered to each patient will be collected with a standardized checklist filled out by the CDPM professionals after each appointment to ensure the fidelity of the intervention [55].

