##### Sample size and statistical power

The required sample size for the randomized clinical trial was calculated for the two main variables (measured with the SEM-CD and the heiQ) with a two-sided α = 0.05 and 80% power. First, for continuous scores, 64 participants in each group will allow to detect a medium effect size (ES=0.5) [75]. In addition, for the heiQ, results are also expressed as the percentage of patients improving at least half a standard deviation. In a before–after study, 35% of patients receiving the intervention presented an improvement of this magnitude [69]. Using these data in a conservative scenario providing for improvement in 20% of control participants, 138 patients are required in each group to detect a 15% difference. Accounting for an anticipated drop-out rate of 15%, 326 patients will be randomized, 163 in each group. A smaller ES of 0.34 will thus be detectable for continuous scores.

Comparison of the 138 subjects in Group A, re-measured at T3 to the same number of subjects selected in the PRECISE cohort, will also allow detection of an ES of 0.34 when measuring mid-term effects (α = 0.05, power = 80%). An additional 15% will also be enrolled in anticipation of withdrawals.

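### Simple randomisation across eight clinics is valid, but clinic-stratified blocks with clinic in the ANCOVA would be a cheap, small improvement

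*Protocol article*

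**What the plan says.** Under Evaluation of effects (objective 2), the protocol article says: "The first step of randomization is the sequence generation using a simple random allocation sequence". Concealment is by sequentially numbered, sealed, opaque envelopes, opened by a research assistant at a central office. No blocking or stratification is mentioned. The reason given for the randomisation process is the proximity of patients within and between clinics. That concerns contamination, not whether the sequence is restricted.

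Under Sample size and statistical power: "Accounting for an anticipated drop-out rate of 15%, 326 patients will be randomized, 163 in each group". The 138 evaluable patients of Group A are used again for the mid-term comparison with the same number of PRECISE cohort members (Group C).

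Under Implementation evaluation (objective 1), the article allows for centre effects, described as "heterogeneity that may be observed and documented between clinics in terms of outcomes produced", and treats them as part of the pragmatic design. It adds that common training of practitioners should reduce them.

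Under Data analysis for the effects, the A-B ANCOVA is adjusted for T1 scores, and for other relevant variables if the groups differ at baseline. Clinic is not named.

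**The concern.** A simple sequence does not control how patients split between Groups A and B within a clinic. If outcomes differ between clinics, part of that difference enters the A-B contrast by chance. The usual standard error covers it, so validity is not at stake, but it is noise that the design could remove.

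A simple sequence also leaves the size of Group A to chance. Group A is the only source for the repeated-measures analysis to T3 and one side of the comparison with Group C, so a shortfall there is not offset by a larger Group B.

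**Working it through.** **Inputs from the article.** 326 randomised, 163 per group; 15% drop-out; two-sided α = 0.05; 80% power; 20% against 35% improving on the heiQ; eight clinics. **Assumptions, not in the article.** Equal recruitment, so 326/8 ≈ 41 patients per clinic (about 35 evaluable after 15% loss); ICC between clinics of 0.02 to 0.10.

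**1. The plan's own figures reproduce.**
- Two proportions, pooled variance, no continuity correction: n = [1.96·√(2·0.275·0.725) + 0.8416·√(0.20·0.80 + 0.35·0.65)]² / 0.15² = (1.2377 + 0.5239)² / 0.0225 ≈ 137.9, so 138 per group.
- Drop-out: 138/0.85 = 162.4, so 163 per group and 326 in total.
- Detectable effect size at 138 per group (t-test): 0.338, stated as 0.34.

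**2. Arm sizes under a simple 1:1 sequence.** Group A size is Binomial(326, 0.5), with SD √(326·0.25) = 9.0.
- P(exactly 163:163) = 4.4%.
- 95% range for Group A: 145 to 181.
- P(Group A ≤ 162) = 48%. At 162, the expected evaluable number is 162 × 0.85 = 137.7, just under 138. At 145 it is 123.

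**3. Effect on the A-B comparison.** Detectable ES = 2.802·√(1/n1 + 1/n2), with 85% of each arm retained.
- 163:163 gives 138.55 and 138.55: ES 0.337.
- 145:181 gives 123.25 and 153.85: ES 0.339.
- Power for 20% against 35% is 80.2% at 163:163, and 79.4% to 80.0% at 145:181 depending on which arm is smaller. Averaged over the binomial split it is 80.1%.

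This loss is negligible.

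**4. Effect on the A-C comparison with Group A at 145.**
- Group C held at 138: 2.802·√(1/123.25 + 1/138) = 0.347.
- Group C reduced to match: 2.802·√(2/123.25) = 0.357.

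Both compare with the stated 0.34.

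**5. Splits within a clinic.** With 41 patients, one arm is Binomial(41, 0.5), 95% range 14 to 27.
- Split of 14:27 or worse: 6.0% in one clinic; 1 − (1 − 0.0596)^8 = 39% in at least one of eight.
- Split of 16:25 or worse: 21% in one clinic; 85% in at least one of eight.

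**6. Avoidable variance.** Set the total variance to 1.
- The clinic share is the ICC, so removing it is worth about 2% to 10% of the sample at ICC 0.02 to 0.10.
- Allowing for only eight clinics, the unadjusted variance is on average (1 − ICC) + (7/8)·ICC. Stratifying and adjusting leaves 1 − ICC. The ratio is 0.98/0.9975 = 0.982 at ICC 0.02 and 0.90/0.9875 = 0.911 at ICC 0.10, a cut of about 2% to 9%.
- Adjusting for clinic while keeping the simple sequence retains on average 1 − 1/35 = 97.1% of the within-clinic information (1 − 1/41 = 97.6% with no loss). The ratios become 0.982/0.971 = 1.01 and 0.911/0.971 = 0.94: no gain at ICC 0.02, about 6% at ICC 0.10.

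Adjustment for T1 scores may already absorb part of any clinic difference, so these are upper figures.

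**The case against.** The strongest reply is that this is a choice between two valid methods. Simple randomisation with concealed, centrally opened envelopes is unbiased. It is also the least predictable option in an open trial where referring professionals choose whom to send and later learn the allocations. Most of the statistical gain at a larger ICC comes from adjusting for clinic, not from blocking. The ICC is not in the article, and a covariate list is commonly left to a fuller document. All of this stands, and it limits the point to a small improvement. It does not remove the point, because the article positively names a simple sequence and the alternative costs little.

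Four stronger readings are tempting but unsupported:
- That the plan expects centre effects. It says only that they may be observed, and that common training should reduce them.
- That simple randomisation defeats the aim of comparable statistical weight for each practice. That aim concerns numbers recruited per clinic, which no allocation method controls.
- That "326 patients will be randomized, 163 in each group" is contradicted by the method. It is a planning figure, the expected result of 1:1 allocation.
- That blocking would remove arm-size imbalance. With blocks of 4, each clinic can end 2 apart, so 16 apart over eight clinics (155:171). With blocks of 6 the limits are 3 and 24 (151:175).

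**Conclusion.** A cheap improvement, not an error. The A-B comparison is unbiased as planned, the sample size reproduces, and power loss from unequal arms is negligible. What can be gained is a reduction in A-B variance of roughly 2% to 10% at an assumed ICC of 0.02 to 0.10, less after T1 adjustment, and a narrower range for Group A than 145 to 181. The A-C cost is small even at the lower end of that range: a detectable effect size of about 0.347, or 0.357 if Group C shrinks equally, against 0.34. The within-clinic figures assume equal recruitment of about 41 patients per clinic. If the word simple was used loosely for a sequence that is in fact restricted, only the text needs correcting.

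**What to change.** Generate the sequence in permuted blocks of randomly varying, undisclosed size, stratified by clinic. Keep one numbered envelope series per clinic, opened at the central office as already planned. Prespecify clinic as a covariate in the A-B ANCOVA, whatever the baseline comparison shows. The total stays at 326.

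If simple randomisation is kept, describe 163 per group as the expected number and still prespecify clinic in the ANCOVA.

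The cost is eight envelope series instead of one, and slightly more predictable allocation in an open, referral-based trial. Varying block sizes and central opening limit that predictability but do not abolish it.

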### Ethical considerations

The project received approval by the research ethics committee of the Centre de santé et de services sociaux de Chicoutimi. Informed consent will be obtained from all participants. For ethical reasons, patients who decline to participate will still be offered the intervention in their clinic. For patients willing to participate, the three-month waiting period for the delayed intervention group (group B) will have a negligible effect, given the chronic nature of their conditions. Informed consent will be sought from each participant for the use of administrative data. Confidentiality will be ensured and the data will be stored according to the rules and recommendations of the research ethics committee.

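### T2 in Group A is counted from a delivered intervention, so a randomised Group A patient who never starts has no T2 date and can drop out of the randomised comparison

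*Protocol article*

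**What the plan says.** All references are to the Protocol article.

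- **The T2 rule.** Evaluation of effects (objective 2) places T2 at "three months after the intervention for Group A or immediately before the intervention for Group B". This is the only sentence in the text that says when the T2 questionnaire is completed.
- **Three-month wording elsewhere in that section.** It says that "T2 measures will enable the assessment of the effect after three months". Its list of aims asks "whether the immediate intervention group (Group A) will have changes at 3 months that are sustained" and "whether there will be changes in the first 3 months before the intervention with Group B". Group B is given a three-month waiting period.
- **T3.** All Group A patients are reassessed one year after T1, whatever they received.
- **Analysis.** Data analysis compares Groups A and B on T2 scores by ANCOVA adjusted for T1.
- **Allowance for loss.** Sample size and statistical power says: "Accounting for an anticipated drop-out rate of 15%, 326 patients will be randomized, 163 in each group".
- **Patients outside the study.** The referral paragraph says "Patients refusing to take part in the study will still be eligible to receive the intervention without being involved in the evaluation process", and Ethical considerations says that "patients who decline to participate will still be offered the intervention in their clinic".

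**The concern.** The randomised comparison needs a T2 score from everyone allocated. In Group A the event that starts the T2 clock is delivery of the intervention, which happens after randomisation and in part reflects the patient's own engagement. If the event does not happen, the sentence supplies no date on which to send the questionnaire.

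The patients at risk of going unmeasured are then the Group A non-starters. Group B has no counterpart, because its T2 comes before any intervention. An A–B contrast without those patients sets people who took up the service against everyone who waited. The trial describes itself as pragmatic, and its question is what happens when the service is offered to referred patients. Dropping non-starters answers a different question and gives up part of the protection that randomisation provides.

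**Working it through.** **1. The plan's own figures.** Inputs from Sample size and statistical power: 35% v 20%, two-sided α = 0.05, power 80%, drop-out 15%.

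- Mean proportion = (0.35 + 0.20)/2 = 0.275.
- n per group = [1.960 × √(2 × 0.275 × 0.725) + 0.842 × √(0.35 × 0.65 + 0.20 × 0.80)]² / 0.15² = (1.238 + 0.524)² / 0.0225 ≈ 138.
- 138 / 0.85 = 162.4, rounded up to 163 per group, 326 in total.
- Detectable effect at 138 per group = (1.960 + 0.842) × √(2/138) = 0.337, or 0.338 with the t distribution. The plan states 0.34.

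The figures reproduce. The allowance for loss is 163 − 138 = 25 patients per arm.

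**2. Who has a T2 date under the text.**

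| Randomised patient | Anchor | Date available? |
|---|---|---|
| Group A, receives the intervention | three months after it | Yes, although start or end of the intervention is not specified |
| Group A, never starts | the same | No |
| Group B, later treated | just before the intervention, after a three-month wait | Yes |
| Group B, not later treated | end of the three-month wait | Yes, by inference from the waiting period |
| Group A at T3 | one year after T1 | Yes, for all |

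Only the Group A non-starter has no date. The T3 row shows that the plan already uses an anchor that does not depend on delivery.

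**3. Does the three-month wording supply the missing date?** The aims and the waiting period suggest a T2 about three months after T1. That does not agree with the Group A rule. Each intervention lasts less than three months, so if the clock runs from its end, T2 in Group A could fall up to about 3 + 3 = 6 months after T1, against about 3 months in Group B. The two descriptions conflict, and neither says what happens to a non-starter.

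**4. Illustrative size.** The documents give no non-start rate. Assume that a share f of Group A is untreated, gains nothing, is otherwise comparable, and is absent from the analysis. The analysis then shows the effect in the treated, taken as 0.34 SD. The effect in all randomised is (1 − f) × 0.34, and the overstatement is 1/(1 − f).

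| f | Effect in all randomised (SD) | Overstatement |
|---|---|---|
| 5% | 0.323 | 5% |
| 10% | 0.306 | 11% |
| 15% | 0.289 | 18% |

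The 15% row borrows the plan's drop-out figure as a convenient upper value; the plan does not call it a non-start rate. If non-starters also differ in prognosis, a further bias is added, and the documents give neither its size nor its sign.

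**The case against.** The strongest reply is that T2 is not defined solely by delivery. The same section repeatedly speaks of three months, and the study timeline (Figure 2), which is not shown in the text available, may give a date. The groups are formed by random allocation, the ANCOVA is described as comparing Groups A and B, and no per-protocol restriction is written anywhere. How missing scores and non-starters are analysed normally belongs in the SAP. The number of non-starters may also be small.

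Much of this stands. It would be wrong to say that T2 is tied only to the intervention, and wrong to say that the plan restricts the analysis to treated patients. The absence of a missing-data method is not a fault in this article.

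Two things survive. The three-month phrases state aims and the length of the wait; they conflict with the operative Group A rule rather than fill its gap, and the text would need reconciling even if Figure 2 shows a date. And a SAP can choose how to analyse scores but cannot recover questionnaires that were never sent because the triggering event did not occur. The co-intervention questionnaire does not help, since it is itself given at T2.

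**Conclusion.** The point holds for Group A. Read literally, the T2 rule gives a randomised Group A patient who never starts no measurement date. It therefore allows selective loss from the A–B comparison and a shift towards the effect in those treated. The figure of 0.29 against 0.34 SD is an illustration that rests on an assumed 15% untreated with no gain; it is not an estimate.

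A reader might infer more, and the documents do not support it:

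- **That waiting patients can leave the study and still be treated.** The sentences on refusing and declining concern people who never join, before T1 and randomisation. Nothing says what a randomised Group B patient who withdraws may receive. Early exit from Group B is at most a possible risk of an unblinded wait-list design. The size and direction of any resulting bias are unknown, so no figure is offered.
- **That stopping before three encounters removes T2.** The three encounters describe the content of the intervention; no sentence makes T2 depend on completing them.
- **That the 15% assumes data missing at random.** It is ordinary sample-size inflation and states no missing-data model.

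**What to change.** In Evaluation of effects (objective 2), replace the T2 sentence with one that:

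1. defines T2 in both arms by the same interval counted from T1 or from randomisation, reconciled with the three-month wording in the aims and with Group B's T2 falling before its intervention;
2. sends the T2 questionnaire to every randomised patient on that date, whether or not the intervention was started or completed, unless consent to follow-up is withdrawn;
3. states that T2 scores are analysed by allocated group.

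Figure 2 should be checked against the new wording. The anchor matters: asking for questionnaires on a planned T2 date does not help a non-starter if that date is still counted from the intervention. The same change removes the conflict over T2 timing between the arms.

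The cost is a few sentences and a few extra questionnaires, no more than about 25 in Group A if the whole drop-out allowance were non-starters. The effect estimate may be smaller, because it would include patients who were offered the service and did not take it up.
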